## Abstract

**Background::**

There is no effective treatment for idiopathic tinnitus. Both acoustic therapy and acupuncture have been used in the treatment of idiopathic tinnitus, but the clinical efficacy is quite different. For there is no clinical study combining the 2, the purpose of this randomized controlled trial is to evaluate the effectiveness and safety of acoustic therapy combined with acupuncture in the treatment of idiopathic tinnitus.

**Methods::**

This is a prospective randomized controlled trial to study the effectiveness and safety of acoustic therapy combined with acupuncture in the treatment of idiopathic tinnitus, and is approved by the clinical research ethics committee of our hospital. The patients are randomly divided into one of 2 treatment options: (A) acoustic therapy combined with acupuncture group and (B) simple acupuncture group. Patients, doctors, nurses, and data collection assistants are blinded to group allocation. Observation indicators include:

Data is analyzed using the statistical software package SPSS version 25.0 (Chicago, IL).

**Discussion::**

This protocol will evaluate the efficacy and safety of acoustic therapy combined with acupuncture in the treatment of idiopathic tinnitus. The results of this experiment will provide clinical evidence for the use of acoustic therapy combined with acupuncture in the treatment of idiopathic tinnitus.

**Trial registration::**

This study protocol is registered in

**Ethics and dissemination::**

Private information from individuals will not be published. This systematic review also does not involve endangering participant rights. Ethical approval was not required.

**OSF Registration number::**

DOI 10.17605/OSF.IO/87VFB.

## Introduction

1

Tinnitus refers to an abnormal sound consciousness in the ear or head of the patients in the absence of an external sound source.^[1]^ With changes in the social environment, more and more people are exposed to the risk factors of tinnitus, making them susceptible to tinnitus. According to reports, the prevalence of tinnitus is 6.6% to 18.6%, and the prevalence of tinnitus among people over 55 has increased to 30%.^[1,2]^ Tinnitus can be caused by organic, non-organic disease or unknown etiology, and can be divided into objective tinnitus and subjective tinnitus. Unexplained subjective tinnitus is also called idiopathic tinnitus.^[3]^ Due to the high incidence of tinnitus, especially persistent annoying subjective tinnitus can cause anxiety, depression and insomnia in patients, and seriously affect the quality of lives of patients.^[4]^ Some patients even choose to commit suicide because they cannot stand the double torments of severe tinnitus interference and physical and mental illness.^[5]^ Due to the complex etiology of tinnitus and the unclear mechanism, there is still no specific treatment method. Therefore breaking through the dilemma of subjective tinnitus diagnosis and treatment and related research and finding an effective treatment method is still one of the challenges the medical community are facing today.

In recent years, based on the maladaptive auditory cortex reorganization theory in the study of tinnitus mechanism, some researchers have achieved certain results in the application of tailor-made notched music (TMNM) to individualized acoustic therapy for tinnitus patients.^[6]^ Acoustic therapy is a physical and non-invasive treatment that is divided into masking therapy which is similar to tinnitus^[7]^ and a custom therapy that diverts attention, temporarily forgetting or listening to the original sound of nature.^[8]^ The current effective rate reports are quite different. Acupuncture is a traditional treatment method in China, which has a long history of application in the treatment of tinnitus. Studies have shown that acupuncture is effective in the treatment of tinnitus, and the efficacy is due to drug treatment,^[9]^ but there are also systematic reviews indicating that the clinical efficacy of acupuncture in the treatment of tinnitus is not clear yet, the difference is large.^[10,11]^

Therefore, this protocol will combine acoustic therapy and acupuncture in the treatment of idiopathic tinnitus, and evaluate the effectiveness and safety of it.

## Materials and methods

2

### Study design

2.1

This is a prospective randomized controlled trial to study the effectiveness and safety of acoustic therapy combined with acupuncture in the treatment of idiopathic tinnitus. This experiment will follow the intervention reporting standards of acupuncture controlled trials^[12]^ and comprehensive trial reporting standards.^[13]^ The flowchart is shown in Figure 1.

**Figure 1 F1:**
[figure not shown]
Flow diagram.

### Ethics and registration

2.2

This research protocol complies with the Declaration of Helsinki and is approved by the clinical research ethics committee of the hospital. This experiment has already been registered in open science framework (OSF Registration number: DOI 10.17605/OSF.IO/87VFB). Before randomization, all patients need to sign a written informed consent and they are free to choose whether to continue the trial at any time.

### Sample size

2.3

The calculation of the sample size is based on the visual analogue scale (VAS) score results. According to the pre-test results, the average score of the experimental group is estimated to be 3.1 and the standard deviation is 1.3. The control group average score is 4.2 and the standard deviation is 1.9. The sample size calculation formula is as follows:$$n=n1=n2=\frac{{\left(u_{a}+u_{\beta }\right)}^{2}\times \sigma^{2}}{\delta^{2}}\times 2$$

At the 5% significance level, a total of 38 patients are required for each group to achieve 80% power. The estimated withdrawal rate is 20%, and 48 patients will be included in each group.

### Patients

2.4

Inclusion criteria:

1.Meet the diagnosis of idiopathic tinnitus^[3]^;2.Over 18 years old;3.Suffering from persistent annoying tinnitus and mainly single tone;4.The course of the disease is over 6 months and the main frequency of tinnitus is 1000 to 8000 Hz;5.With or without hearing loss, no severe hearing loss in the octave band centered on the main frequency of tinnitus (≤70 dB HL).

Exclusion criteria:

1.Ear diseases with a clear cause;2.Objective tinnitus;3.Pure tone audiometry showed conductive or mixed hearing loss;4.Suffer from serious systemic diseases (mental and psychological diseases, cervical spondylosis, etc.);5.Those who cannot understand the research plan after explanation, or are unwilling to participate or have poor compliance.

### Study design

2.5

Eligible participants are randomly assigned to the treatment group or the control group at a ratio of 1:1 using a random tool based on the central network.^[14]^ Randomization is performed without any stratification and generated by an independent statistician who is not involved in trial implementation or statistical analysis using SAS 9.3 software (SAS Institute, Cary, NC, USA). The clinical research coordinator enter the participant information on the tablet, and is given a random number. The research assistant gets the participants assignment from the computer. Throughout the research process, the research assistant is responsible for screening, recruiting participants, and assigning random number to the included participants. The result assessor is responsible for the assessment of the scale. All of the doctors, researchers, research assistants, participants, intervention supervisors, and statisticians, the grouping of personnel are unknowable.

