### Intervention

2.7

Therapy group:

1.Music intervention: Distribute customized players with left and right sound channels and over-ear headphones to patients, instruct patients to choose a comfortable loudness and focus on listening in an environment without external sound interference. Continuous or intermittent listening is not less than 2 hours a day for 3 consecutive months.2.Acupuncture intervention: the patient takes an appropriate position, fully exposes the surgical site, and locally disinfects the acupuncture site (Ermen, Tinggong, Tinghui, Yifeng, Zhongzhu, Xiaxi, Hegu, Taichong. Take the affected side), an acupuncturist with a Chinese medicine practice license and at least 3 years of clinical experience will perform acupuncture operations.

The acupuncture technique is stimulated for 10 seconds to achieve a sense of “deqi”. The needle is retained for 30 minutes, 3 times a week. The course of treatment lasts 3 months.

The control group will be treated with acupuncture alone, and the treatment plan will be the same as that of the treatment group.

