### Evaluation criteria and efficacy judgment

2.8

1.Tinnitus handicap inventory (THI)^[16]^: The THI scale is divided into 5 levels based on the total score. Grade I: Mildly affects life (0–16 points); Grade II: Slightly affects life (18–36 points); Grade III: Moderately affects life (38–56 points); Grade IV: Severely affects life (58–76 points); Grade V: Extremely affects life (78–100 points). The higher the grade, the more serious the degree of tinnitus. Those with a THI score of above 38 are considered moderate and severe tinnitus patients. Efficacy criteria:1.Cure: THI score dropped to less than 16 points;2.Significantly effective: THI score decreased value ≥17 points;3.Invalid: THI score decreased by <17 points, or even increased.^[17]^2.The visual analogue scale (VAS) marker scale is increased from 0 to 10 points one by one. It is up to the patient to judge the tinnitus loudness and the corresponding tinnitus influence expression map. The higher the score, the greater the tinnitus loudness and its influence. The larger is used to compare the changes in tinnitus loudness values before and after treatment for each patient.3.Adverse reactions: Including intolerance during treatment, dizziness caused by acupuncture, etc.

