## Discussion

3

Severe tinnitus can affect the patients ability to work, lead to a decrease in the quality of life, and even suicidal tendencies.^[18]^ Its pathogenesis is currently unknown, and may be related to peripheral diseases, central and neuroplasticity, emotional disorders, and the patients mental state. Tinnitus treatment has made great progress in the past 10 years, and there are many existing treatment methods, such as masking, transcranial magnetic stimulation treatment, habituation treatment, medicine, acupuncture, etc., but the effect is not very satisfactory.^[19]^

Acoustic therapy is based on centralization theory. Customized music can increase the release of hypothalamic neurotransmitter dopamine and affect the level of 5-hydroxytryptamine in the brain. By adjusting the level of neurotransmitter in the body, the input pathway can be biased to reduce non-auditory signals. The effect of the joint reduction of the limbic system and parahippocampal gyrus (emotion and memory) on centralizing tinnitus.^[20,21]^ In addition to relying on the traditional meridian theory, the mechanism of acupuncture and moxibustion for the treatment of tinnitus, modern research has confirmed that it is also related to the neurophysiology of the olive cochlear nucleus,^[10]^ the atypical upregulation subcortical auditory pathway, the limbic system and the amygdala,^[22]^ and the plasticity of the nervous system^[23,24]^ and so on. The 2 treatments have been applied in clinical practice, but the clinical efficacy is not satisfactory, so we try to combine the 2 treatments to treat specific tinnitus.

This study also has the following limitations: Because this is a single-center randomized controlled study, the included population is regionalized, and the results may be biased; Due to the treatment method, this study cannot achieve strict double-blind and the observation indicators are highly subjective, which may have certain impact on the results.

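### The Abstract and section 2.5 state that participants and research assistants are blinded; the design unmasks participants, and section 2.5 has the research assistant retrieve the assignment

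*Protocol article*

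**What the plan says.** The protocol article makes two broad blinding claims. The Abstract (Methods) says: "Patients, doctors, nurses, and data collection assistants are blinded to group allocation". Section 2.5 (Study design) goes further: "All of the doctors, researchers, research assistants, participants, intervention supervisors, and statisticians, the grouping of personnel are unknowable".

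Three other places bear on these claims:

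- Section 2.5 itself, on how the allocation is obtained: "The research assistant gets the participants assignment from the computer". The same role screens, recruits and assigns random numbers.
- Section 2.7 (Intervention), on the treatment arm: "Distribute customized players with left and right sound channels and over-ear headphones to patients", with the exposure set as "Continuous or intermittent listening is not less than 2 hours a day for 3 consecutive months". On the other arm: "The control group will be treated with acupuncture alone".
- Section 3 (Discussion), in the limitations: "Due to the treatment method, this study cannot achieve strict double-blind and the observation indicators are highly subjective".

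On who rates the outcome, section 2.8 says of the VAS: "It is up to the patient to judge the tinnitus loudness and the corresponding tinnitus influence expression map". Section 2.3 bases the sample size on the VAS.

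**The concern.** The two arms share the same acupuncture plan and differ only in the music. A patient either has the player and a daily listening task or does not, and no substitute is described for the control arm. A claim that participants do not know their group does not fit that design. A claim that the research assistant does not know it does not fit the assistant's own task.

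What is at stake is how the result will be read. The VAS and THI come from the patient, and only one arm receives the additional daily treatment. Any response to expectation or attention therefore enters the difference between groups and cannot be told apart from an effect of the notched music. The Abstract and the methods section are where a reader, or someone assessing risk of bias for a systematic review, looks for the level of blinding. If the trial report carries these statements forward, it will credit the main outcomes with a protection they do not have.

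**Working it through.** No arithmetic decides this point. The check sets the blinding claims beside what the article says each role does.

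| Role | Claimed unaware in | What the article says about the role | Result |
|---|---|---|---|
| Participants | Abstract; 2.5 | One arm gets player, headphones and daily listening; the other gets acupuncture only (2.7) | Claim false |
| Research assistant | 2.5 | Retrieves the assignment from the computer (2.5) | Claim contradicts its own section |
| Staff who hand out players or rework the music | Not named as such; may fall under the general terms | Distribute and instruct (2.7); re-match and reprocess the music if the frequency changes during treatment (2.6.3) | Cannot be unaware for the patients they serve |
| Doctors, including acupuncturists | Abstract; 2.5 | Same acupuncture in both arms; listening is with a personal player (2.7) | Open: masking possible, no means described |
| Result assessor, data collectors | Data collection assistants in the Abstract; assessor perhaps under researchers in 2.5 | Assess the scales (2.5); collect data at monthly visits (2.9) | Open: masking feasible |
| Statisticians | 2.5 | No contact with patients described | Masking feasible |

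1. Participants. Written consent comes before randomisation (2.2), and people who cannot understand the research plan once it is explained are excluded (2.4). Participants therefore know what is being compared. Someone who knows the plan and does or does not receive a player knows the arm.

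2. Research assistant. Retrieving an assignment and being unaware of it cannot both hold, and both statements stand in section 2.5.

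3. Outcomes. The VAS is the patient's own judgement, and the THI is scored from the patient's answers. Masking the person who hands over the form does not mask the person who answers it. Step 1 therefore leaves both scales unmasked, whatever the status of the assessor.

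4. Weight in the trial. The sample size (38 per group, raised to 48 for 20% withdrawal) is built on VAS means of 3.1 and 4.2, a planned difference of 4.2 − 3.1 = 1.1 points. The outcome that sizes the trial is thus one of those affected, in all 2 × 48 = 96 planned participants.

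5. The article's own view. The Discussion says that strict double-blinding is not achievable because of the treatment method, and that the observations are subjective. That agrees with steps 1 and 3 and contradicts the Abstract and section 2.5.

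**The case against.** The strongest reply is that the authors already disclose the problem. The Discussion names both the lack of strict double-blinding and the subjectivity of the outcomes, and says the results may be affected. On that view only loose wording remains. This partly stands: the limitation is not hidden, and the defect is a contradiction rather than a concealment. It does not clear the two statements, which name participants outright and stand in the places readers consult for blinding.

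A second reply is that the awkward sentence in section 2.5 may have been meant as allocation concealment before assignment. The Abstract does not allow that reading, since it speaks of people being blinded to group allocation. If concealment was meant, the text still has to be changed to say so.

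Third, an add-on comparison without a sham is a legitimate design. That stands in full. The fault is in the property claimed for the design, not in the choice of comparator.

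A reader might also infer that doctors and acupuncturists are shown to be unblinded. The article does not support that. Acupuncture is the same in both arms, the listening is with a personal player, and nothing says the acupuncturist supplies it or sees it used. Their unblinding is likely but not shown. Nor is it an error in itself that the result assessor is absent from the list in section 2.5. The terms used there and in the Abstract may cover that role, and a condensed article need not name everyone.

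**Conclusion.** The point holds for participants and for the research assistant. For participants, the blinding statements in the Abstract and section 2.5 are false as written, given section 2.7 and the Discussion. For the research assistant, section 2.5 contradicts itself. As a result the VAS, which drives the sample size, and the THI are both unmasked.

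This rests on one reading: that the control arm receives no player or listening task. Section 2.7 says acupuncture alone and describes no substitute.

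A reader might want to express the bias as a share of the planned 1.1-point difference. The documents give no expectation effect from which to do that, and any percentage would be arithmetic on a chosen number. The direction of concern is clear, since only one arm has the extra treatment, but the size is unknown. The conclusion does not depend on it.

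**What to change.** Replace the blinding statements in the Abstract and section 2.5 with a single one that goes role by role, for example:

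*Participants, the research assistant who obtains the assignment, and staff who supply the players or process the music are not blinded. The result assessor, the data collectors and the analysing statistician are masked to group. Acupuncturists are masked only where they are kept unaware of whether a patient receives the music. VAS and THI are reported by unblinded patients.*

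Before keeping acupuncturists among the masked, the investigators should confirm that a practical means of keeping them unaware exists. If there is none, that sentence should say so.

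Assign scale administration and data entry to existing staff who have no access to the allocation, and say so in sections 2.5 and 2.9. Section 2.9 has 1 or 2 assistants collecting all the data. It should be made clear that they are not the research assistant who obtains assignments. This does not mask the patients' answers; it only makes the claim for the data collectors true.

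In the trial report, describe the VAS and THI effects as unblinded, in line with the Discussion.

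The cost is a change of wording in two places and some division of tasks among existing staff. No treatment, endpoint, sample size or analysis changes. The stated level of blinding becomes less favourable, but accurate.

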### Intervention before treatment

2.6

#### Listening test

2.6.1

Audiology inspections are all completed in a standard sound insulation room. The inspection items are pure tone hearing threshold, acoustic immittance, and distortion product otoacoustic missions (DPOAE).

#### Tinnitus test

2.6.2

1.Main tinnitus frequency test: match the patients description of the main tinnitus tone, and obtain the audio that is most similar to the main tinnitus frequency;2.Tinnitus loudness test: the single-ear sound balance method is used to gradually increase or decrease the intensity of the test tone until it can mask the tinnitus sound, which is the loudness value of the tinnitus matching^[15]^;3.Based on stability considerations, the selected patients are revised and matched again before start of treatment.

#### Music processing

2.6.3

The selected music is based on the patient's favorites, 20 familiar music (high-definition, uncompressed, non-defective source code format) is selected from the music network library established by the researcher, and MATLAB coding language is used to perform digital notch filtering on the selected music. Patients with different main frequencies of bilateral tinnitus matching are treated separately for the left and right ears. If the patients tinnitus frequency changes during treatment, it needs to be matched again and the music should be processed accordingly.

### Intervention

2.7

Therapy group:

1.Music intervention: Distribute customized players with left and right sound channels and over-ear headphones to patients, instruct patients to choose a comfortable loudness and focus on listening in an environment without external sound interference. Continuous or intermittent listening is not less than 2 hours a day for 3 consecutive months.2.Acupuncture intervention: the patient takes an appropriate position, fully exposes the surgical site, and locally disinfects the acupuncture site (Ermen, Tinggong, Tinghui, Yifeng, Zhongzhu, Xiaxi, Hegu, Taichong. Take the affected side), an acupuncturist with a Chinese medicine practice license and at least 3 years of clinical experience will perform acupuncture operations.

The acupuncture technique is stimulated for 10 seconds to achieve a sense of “deqi”. The needle is retained for 30 minutes, 3 times a week. The course of treatment lasts 3 months.

The control group will be treated with acupuncture alone, and the treatment plan will be the same as that of the treatment group.

### Evaluation criteria and efficacy judgment

2.8

1.Tinnitus handicap inventory (THI)^[16]^: The THI scale is divided into 5 levels based on the total score. Grade I: Mildly affects life (0–16 points); Grade II: Slightly affects life (18–36 points); Grade III: Moderately affects life (38–56 points); Grade IV: Severely affects life (58–76 points); Grade V: Extremely affects life (78–100 points). The higher the grade, the more serious the degree of tinnitus. Those with a THI score of above 38 are considered moderate and severe tinnitus patients. Efficacy criteria:1.Cure: THI score dropped to less than 16 points;2.Significantly effective: THI score decreased value ≥17 points;3.Invalid: THI score decreased by <17 points, or even increased.^[17]^2.The visual analogue scale (VAS) marker scale is increased from 0 to 10 points one by one. It is up to the patient to judge the tinnitus loudness and the corresponding tinnitus influence expression map. The higher the score, the greater the tinnitus loudness and its influence. The larger is used to compare the changes in tinnitus loudness values before and after treatment for each patient.3.Adverse reactions: Including intolerance during treatment, dizziness caused by acupuncture, etc.

